**Fig. 1 Fig1:**

Constitution of the exposed versus non-exposed groups of cases who developed haematological malignancy before the age of 7 years and registered in The Danish Cancer Registry (Objective 1)

The incidence of childhood haematopoietic neoplasms among 1,101,055 individuals from the period before the iTFA legislation born between January 1st, 1988 and August 31st, 2004, will be compared to the incidence of childhood haematopoietic neoplasms among 276,422 individuals from the period after the iTFA legislations born between September 1st, 2004 and December 31st, 2008, as a proxy of iTFA gestationally exposed or not exposed, respecitvely. In this overall time period approximately 740 incident haematopoietic neoplasms cases occurred in children before the age of 7 years.

*The second objective* is a case-control study investigating biomarkers of neonatal trans-fatty acid concentrations from stored DBS [34] from individuals who developed childhood haematopoietic neoplasms before the age of 7 years and born in the period 1988–2008 compared to matched controls (Fig. 2).

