**Fig. 2 Fig2:**
[figure not shown]
Flow chart of the matched case-control study (Objective 2)

Since 1981, routinely collected DBS samples taken by heel prick 48–72 h after birth have been collected for all new-born in Denmark. DBS cards are stored in the Biological Specimen Bank for Neonatal Screening at Statens Serum Institute and have been made available to the project [36].

For each case with haematopoietic neoplasms, a control, individually matched for gender, exact date and year of birth, mother’s parity, place of birth, being alive and with no diagnosis of cancer, will be selected and fatty acids isomers measured in the DBS. A case is defined as a child, less than 7 years, with a cancer diagnosis (ICD-10 DC81-C96) and without a DS diagnosis [37]. If more than one participant meets the matching criteria a random control from the eligible participants will be selected. If no participant meets the matching criteria the criteria for exact date of birth or place of birth will be relaxed as needed to match controls to cases and the adjustments made will be reported.

Previous studies have confirmed that storage time of DBS as long as 20 years do not bias inter-individual variation in concentrations of vitamin D and possible other fat soluble substances [38]. Furthermore, as date of birth is used as matching criterion for the controls, potential degradation of TFA would affect equally cases and controls and is therefore unlikely to bias the results.

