The methodology for measuring biomarkers of fatty acids in DBS has been set up at the International Agency of Research of Cancer (IARC) in Lyon, France, a specialized WHO and UN organization. The DBS will securely be transported from Denmark to IARC, Lyon, France, where they will be kept in a − 80 °C freezer until analysis. Our validated gas chromatography methodology allows a complete separation, identification and quantification of sixty fatty acids from short-chain saturated to long-chain polyunsaturated fatty acids, including fifteen individual isomers of industrial trans fatty acids (elaidic acid, trans n-6 and n-3 PUFA) separated from natural trans fatty acids (CLA, vaccenic acid) in one-hour runs. The laboratory involved in the set up at IARC is at the cutting edge of lipidomic technologies and have developed sound and innovative high-throughput methods for fatty acid measurements [20]. Fatty acid concentrations will be determined in plasma phospholipids, as some specific fatty acids measured in this lipid fraction have been shown to be reliable biomarkers of specific dietary intakes, as well as fatty acid metabolism [39–41]. Samples from cases and their matched controls will be analysed within the same daily batch, with two quality controls in each batch. The technical staff will not have any information on the case/control status. Total lipids will be extracted from plasma samples with chloroform-methanol containing antioxidant butylated hydroxytoluene and L-A-phosphatidylcholine-dimyristoyl-d as an internal standard. Phospholipids will be purified by adsorption chromatography; fatty acid methyl esters will be separated through gas chromatography. The relative amount of each fatty acid, expressed as percent of total fatty acids, will be quantified by integrating the area under the peak and dividing the result by the total area. Fatty acids will also be expressed as absolute concentrations in plasma (μmol/l) based on the quantity of the methyl deuterated internal standard.

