Based on this methodology, coefficients of variation (CVs) for fatty acids have been calculated for 60 samples. CVs ranged from 0.013% for large peaks to 7.75% for the smallest peaks (less than 0.10% of total fatty acids). Overall CVs (within-batch and between batch CVs) are very good for iTFA isomers, mainly for elaidic acid (CV = 0.137%). Overall CV is 0.122% for total iTFA. CVs for rTFAs are also good, mainly for vaccenic acid, the main iTFA isomer (CV = 0.282%). CV for total iTFA is 0.123%.

Because the TFA levels in the new-born blood also reflects the TFA status of the mother at the end of pregnancy, measurement of iTFA levels in DBS will furthermore serve as validation for the effect of trans-fat elimination for incident cases.

To take into account different cohort effects or changes in life-style in the period 1988 to 2008, we will merge the cohort data with information from the Danish Medical Birth Registry on trends in co-variates which might have changed during the time period, e.g. smoking during pregnancy and age of the mother.

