Nevertheless, the proposed study design, especially in the first objective, also implies some uncertainties, including a potential ecological fallacy. The exposure measure is applied equally to all members of the cohort before and after the ban, while the individual exposures have probably differed. However, a previous study has shown a marked decline of average iTFA intake resulting in elimination after the ban [32]. In the case-control study we investigate TFA exposure individually in all cases from 1988 to 2008. The variations in the exposure observed in the case-control study will then inform our assumptions taken in the cohort study.

Any societal changes preceding 1988 or succeeding 2008 will influence the exposed and control groups similarly, while results will be confounded by any potential societal changes occurring around the time where the trans-fat ban was implemented (e.g. 2003/04). However, we are unaware of such changes except for a screening for DS which we have taken into account by excluding children with DS.

Potentially exposure to TFA from maternal adipose stores could affect the “unexposed” group (born after the ban of iTFA) and postnatal influences like maternal feeding practice and weight gain, may also influence cancer risk through a non-TFA mechanism. Although this may indeed seem a possible limitation, since literature has shown that weight loss of the mother (e.g. during lactation) liberates TFA fat deposits [44], proper randomization in our societal experiment study is mimicked by separating exposed and non-exposed individuals by one point in time with a minimum of selection bias. Thus, it is an obvious strength to the present research design, that the individuals will be unselected, and generally representative of the Danish population, in relation to exposed vs. non-exposed to the trans-fat legislation, as well as to the development of haematopoietic neoplasms. However, since we do not know the exact mechanism between TFA and childhood neoplasms, we cannot account for a residual confounding which might affect observed associations. Residual confounding could be caused by additional components in food products with high contents of TFA. We are not able to investigate TFA levels at specific developmental stages during gestation, but since no knowledge exist on specific target windows for childhood cancers, this may not be relevant.

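### Blood-spot iTFA is meant to validate the ban, but spot storage age is set by birth date, and the article's storage argument covers only the matched case-control contrast

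*Protocol article*

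**What the plan says.** All references are to the protocol article. Methods, Study population, places the matched case-control study in children "born in the period 1988–2008 compared to matched controls". Heel-prick spots are collected two to three days after birth and stored. The post-ban cohort is those "born between September 1st, 2004 and December 31st, 2008".

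The same section states that "measurement of iTFA levels in DBS will furthermore serve as validation for the effect of trans-fat elimination for incident cases". The Discussion builds on this: "The variations in the exposure observed in the case-control study will then inform our assumptions taken in the cohort study".

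Two arguments about storage are offered. The first is "Previous studies have confirmed that storage time of DBS as long as 20 years do not bias inter-individual variation", said of vitamin D and, possibly, other fat-soluble substances. The second is that matching on birth date makes any degradation equal for cases and controls. If no control fits, "the criteria for exact date of birth or place of birth will be relaxed as needed", and the adjustments are to be reported.

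The assay is introduced as set up for dried blood spots, but the description then reads "Total lipids will be extracted from plasma samples with chloroform-methanol" and reports plasma concentrations. The CVs come from 60 samples whose matrix is not named. Total iTFA has a CV of 0.122% in one sentence, and two sentences later "CV for total iTFA is 0.123"%. Vaccenic acid is listed as a natural trans fatty acid and then called the main iTFA isomer.

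**The concern.** Objective 1 has no individual intake data. Birth before or after September 2004 stands in for exposure, and the blood spots are the study's own check on that proxy. Validating an effect of the ban means comparing iTFA in children born before it with iTFA in those born after it. In that comparison storage time differs systematically between the groups, and date matching cannot help because both members of a pair lie on the same side.

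The stated validation sample is also the incident cases, who are selected on the outcome. If the study hypothesis is true, their iTFA is higher than that of the cohort whose exposure is to be checked.

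Depending on the direction of drift, the study could report that exposure did not fall when it did, or credit the ban with a fall that arose in the freezer.

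**Working it through.** **The plan's own figure.** The article gives no sample size or precision for the validation. The only figure for the blood-spot study is the least detectable OR of 1.35 to 1.75 with 700 pairs and 80% power. A matched-pair (McNemar) calculation, two-sided 5%, zero within-pair correlation, gives 1.58, 1.35 and 1.76 at control exposure of 10%, 50% and 90%. The stated range reproduces; the point below does not depend on it.

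**Storage gap.** Inputs: births 1 January 1988 to 31 December 2008, cut at 1 September 2004 (2004.67), births taken as uniform in time.
- Pre-ban midpoint: (1988 + 2004.67)/2 = 1996.33.
- Post-ban midpoint: (2004.67 + 2009)/2 = 2006.83.
- Gap: 10.5 years, whatever the assay date.

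**Reach of the 20-year evidence.** When the registry data close at the end of 2015, birth years 1988 to 1995 are past 20 years: 8/21 = 38% of birth years, all pre-ban. The assay date is not given. If it lies between 2016 and 2020 (assumed), 48% to 72% of pre-ban birth time and none of the post-ban time is past 20 years.

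**Identifiability.** With a single assay date, storage age is assay date minus birth date, so their correlation is −1. A linear trend in exposure cannot be separated from linear storage drift. A step at the cut can be, in part: its correlation with storage age is −0.70, so the variance inflation is 1/(1 − 0.70²) ≈ 2.0.

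**Size of the mixing.** Let the measured value drift at rate r per storage year (log scale) with constant true exposure. Averaging over each period, whose half-lengths are 8.33 and 2.17 years,

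post/pre = exp(−10.5r) × [sinh(2.17r)/(2.17r)] ÷ [sinh(8.33r)/(8.33r)].

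For r = −0.03: 1.370 × 1.0007/1.0104 = 1.36.

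For births January 2001 to March 2003 versus October 2004 to December 2006, the midpoints are 2002.125 and 2005.875, a gap of 3.75 years. The windows are equally long, so the ratio is exp(−3.75r).

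| Assumed drift per storage year | Post/pre ratio, all births | Post/pre ratio, narrow windows |
|---|---|---|
| −3% | 1.36 | 1.12 |
| −2% | 1.23 | 1.08 |
| −1% | 1.11 | 1.04 |
| +1% | 0.90 | 0.96 |
| +2% | 0.81 | 0.93 |
| +3% | 0.72 | 0.89 |

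The documents give no drift figure; the range is an assumption.

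**Samples in the narrow windows.** With 700 to 740 controls over 21 birth years, each 2.25-year window holds 700/21 × 2.25 = 75 to 740/21 × 2.25 = 79 controls.

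**The case against.** A reader might infer that blood spots cannot show that exposure fell. The documents do not support that. Plain loss of TFA in old spots lowers the pre-ban values, so a fall seen on the absolute scale would be conservative. A false fall needs upward drift, most plausible on the percent-of-total scale if other fatty acids are lost faster, which is itself an assumption. A step at the cut is also only partly tied to linear drift, although the Background describes a general decline in iTFA use alongside the ban, which blurs a step. The Discussion also cites an earlier study showing a marked decline in intake, so the exposure assumption does not rest on the spots alone. If that decline is large, drift of a few percent a year may not mask it.

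The validation is one sentence and fixes no contrast, window or adjustment; a fuller document may do so. That is fair, and lack of such detail is not the complaint. What stands is what the article states: a validation in cases, supported by a storage argument that does not reach it.

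On cases, the point is limited. If their iTFA is higher in both periods, the contrast within cases need not be biased, and controls are assayed anyway.

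It is also tempting to say that relaxing the date match destroys its protection. It does not. Relaxation applies only when nobody matches, and it is reported. With 1,377,477 births in 21 years, about 180 a day, place may well be the binding criterion. A one-week relaxation at 1% a year moves values by 7/365 × 1% ≈ 0.02%.

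Nor can the CVs be called plasma CVs as a fact, since the matrix is unnamed. A CV describes random error and does not confound period with storage, so the assay wording is a separate matter.

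**Conclusion.** The point holds in a limited form. The storage argument covers the matched case-control contrast and not the use of blood-spot iTFA to validate the ban. An unadjusted before/after difference is open to storage drift in either direction: a ratio of 1.11 to 1.36 under loss, or 0.90 to 0.72 under upward drift, with no true change. This rests on births spread evenly over time and on an assumed drift of 1 to 3% a year. The 10.5-year gap does not depend on the assay date or the drift rate.

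The odds ratios of Objective 2 are not affected, because members of a pair share their storage age. The change should be made, since the validation feeds the interpretation of Objective 1 and better material is already to be measured. The plasma and labelling contradictions are smaller and stand on their own.

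**What to change.** 1. Run the validation in the controls, who are already assayed and not selected on the outcome.
2. Compare births shortly before and after the phase-in, for example January 2001 to March 2003 versus October 2004 to December 2006. This cuts the storage gap from 10.5 to 3.75 years.
3. Contrast the iTFA change with the change in ruminant TFA from the same run. It shares the storage age, and the order as described limits only iTFA. State the assumption that the two behave alike in storage.
4. Report percent of total fatty acids and absolute concentration. Keeping only the relative scale would leave the one most open to a false fall.
5. When matching, relax place of birth before date of birth, and let no pair cross the phase-in.
6. Reconcile the plasma wording with the dried-blood-spot samples and state the matrix of the 60 samples and of the batch quality controls. Correct the labels: vaccenic acid as an iTFA isomer, and the two CVs for total iTFA.

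The cost is wording and a short extra analysis of planned measurements. The narrow windows leave about 75 to 80 controls per side, so the estimate is less precise. If the 60 samples prove not to be blood spots, precision must be shown for blood spots, and the CVs may look less favourable.

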### Power calculation

Using the command stpower for the log-rank test for comparison of two survival functions in Stata 14 we calculated the least detectable hazard ratio (exposed versus unexposed) to be 1.35 assuming 80% power and a significance level of 5% in objective 1 (the cohort study) [42].

In objective 2 (the case-control study) we have a sample size of 700 cancer cases and 700 controls, and assuming 80% power, the least detectable OR will be between 1.35 and 1.75, depending on the exposure among the controls (10–90%). The power analysis for the matched 1:1 case-control study was performed using the power mcc command in Stata 14 [43].

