### Statistical analysis

In objective 1 we will use a Cox proportional hazard model with age as the underlying timescale to investigate the hazard of childhood haematopoietic neoplasms in children born before and after the iTFA ban, as a proxy for iTFA exposed or not exposed in fetal life. Observations will be censored in case of death, immigration or at 7 years of age. To take the potential secular trend in the incidence of haematopoietic neoplasms into account we will model the variation in cancer risk across birth cohorts by a piecewise linear spline with a knot at 1st of September 2004. Further, we will investigate incidence trends over time.

By examining *all* children from the entire national birth cohorts it is reasonable to assume that all confounding variables will be equally distributed among the exposed and non-exposed individuals, but still we will investigate potential influence of secular variation or possible confounding effects which might have changed during the time period and which might be associated with both TFA exposure and haematopoietic neoplasms. Such potential confounders could be age of the mother at the time of giving birth, assuming accumulation of TFA with age and an older age for first time pregnancies over time. The median gestational age might have increased during the investigated time period, which would increase the average intrauterine exposure to TFA over the study period [44]. Smoking status during pregnancy might have decreased over time and smoking might be associated with increased cancer risk, smoking is also associated with gestational age and thereby with the length of the TFA exposure during pregnancy.

As sub-analysis we will exclude cancer cases diagnosed before the 90 day of life since the origin most likely is due to chromosomal alterations leading to oncogene activation [37]. If feasible we will investigate the first born only since some studies have shown higher risk of childhood cancers in the first born compared to their younger siblings [45] and sensitivity analysis of sub-types of haematopoietic neoplasms (leukemia and lymphoma). Further, we will investigate children with early diagnosis, e.g. before age 4 years.

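### The objective 1 detectable hazard ratio of 1.35 belongs to an unadjusted log-rank test, not to the trend-adjusted Cox model that is planned

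*Protocol article*

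**What the plan says.** The *Power calculation* section of the Protocol article names its test: "Using the command stpower for the log-rank test for comparison of two survival functions in Stata 14". From this it reports that "we calculated the least detectable hazard ratio (exposed versus unexposed) to be 1.35 assuming 80% power", with "a significance level of 5% in objective 1 (the cohort study". No covariate or trend term is mentioned there.

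The legend to Fig. 1 in *Study population* gives the groups as "1,101,055 individuals from the period before the iTFA legislation born between January 1st, 1988 and August 31st, 2004" and "276,422 individuals from the period after the iTFA legislations born between September 1st, 2004 and December 31st, 2008", and says that "approximately 740 incident haematopoietic neoplasms cases occurred in children before the age of 7 years".

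The *Statistical analysis* section plans a Cox model on the age scale comparing children born before and after the ban. To deal with secular trend it adds: "we will model the variation in cancer risk across birth cohorts by a piecewise linear spline with a knot at 1st of September 2004". *Hypotheses and objectives* likewise words the objective 1 hypothesis as a before/after difference that allows for underlying trends in these cancers.

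**The concern.** Before/after status is fully determined by birth date, so any birth-cohort trend term competes with it for the same information. The competition is strongest when the trend may change slope at the very date that defines exposure. A detectable effect computed with no trend term then says little about what the adjusted model can detect.

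The cohort is fixed, so what is at stake is interpretation. Someone who relies on 80% power at 1.35 could take a null adjusted result as fair evidence against an effect of that size, although the adjusted analysis would probably have missed it.

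**Working it through.** **Inputs.** From the Fig. 1 legend: 1,101,055 births before the cut, 276,422 after, about 740 events. From *Power calculation*: 80% power, 5% level. Follow-up is the same for all: "Observations will be censored in case of death, immigration or at 7 years of age". Assumed, because the document does not say: two-sided test, births spread evenly within each period, flat underlying incidence.

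**Step 1: reproduce 1.35.**
- Share born after the cut: p = 276,422 / 1,377,477 = 0.2007.
- Schoenfeld: SE = 1/√(740 × 0.2007 × 0.7993) = 0.0918; detectable HR = exp(2.80 × 0.0918) = 1.29.
- Freedman, with r = 276,422/1,101,055 = 0.2511 and h = after/before HR: events = 2.80² (1 + r h)² / [r (1 − h)²]. With 740 events, h = 0.755, that is 1.32 as before/after. For h = 1/1.35 the formula needs 654 events.
- Seven-year event-free survival is 1 − 740/1,377,477 = 0.99946. If it was rounded to 0.9995, Freedman returns h = 0.7405, that is 1.35. The rounding is an inference, but it recovers the stated value.

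So 1.35 is a correct and slightly cautious figure for an unadjusted test.

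**Step 2: before/after term plus spline.** With a free slope on each side of the knot, the before/after term is the jump at the knot. For even births, its variance is four times the unadjusted variance.
- Null information: SE = 2 × 0.0918 = 0.184.
- True after-ban rate 1/1.35 of the before-ban rate: after-ban events = 740 × (276,422/1.35) / (1,101,055 + 276,422/1.35) = 116, leaving 624 before; unadjusted SE = √(1/116 + 1/624) = 0.101; adjusted SE = 0.202.

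Power = Φ(ln 1.35/SE − 1.96), detectable HR = exp(2.80 × SE), and ln 1.35 = 0.300.

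| Model | SE | Power at 1.35 | Detectable HR |
|---|---|---|---|
| Unadjusted | 0.092–0.101 | 84–91% | 1.29–1.33 |
| Before/after term + spline | 0.184–0.202 | 32–37% | 1.67–1.76 |
| Before/after term + one linear trend (not planned; for comparison) | 0.128–0.133 | 61–65% | 1.43–1.45 |

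The last row follows from a squared correlation of 0.48 between before/after status and linear birth date, which gives a null variance inflation of 1/(1 − 0.484) = 1.94. If the after-ban rate were higher instead, the adjusted powers would be 43% (spline) and 67% (linear).

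**Step 3: continuous spline with no before/after term.** The only term tied to the ban is the change in slope.
- A true constant step of 1/1.35 projects onto a slope change of −0.083 per year with SE 0.050. Power = Φ(0.083/0.050 − 1.96) = 38%.
- An effect growing linearly on the log scale after the knot and averaging 1.35 has slope 2 × 0.300/4.33 years = 0.139 per year. With SE 0.052 (lower after-ban rate) power is 76%; with the null SE of 0.046 it is 85%.

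**Check.** A Poisson simulation on 252 birth months (1,500 runs, after-ban rate 1/1.35) rejected in 86% of runs unadjusted, 61% with one linear trend, 28% with before/after term plus spline, and 37% for the slope change.

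**The case against.** Several points on the other side are fair.

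- **Is 1.35 an arithmetic mistake?** A reader might infer so. It is not: the section names its test, and the figure reproduces for that test.
- **Does the planned model have a known power of 32–65%?** A reader might infer that too, but the document does not fix the model that far. *Statistical analysis* plans no single linear trend, so 61–65% belongs to a simpler model shown only for comparison. It also does not say whether a before/after term stands beside the spline, so 32–37% is conditional on that reading.
- **Could the planned model do better?** Yes, for a gradual effect. The slope-change test has about 76–85% power for the growing effect in Step 3, and the *Discussion* raises release of trans-fat from maternal stores after the ban. But that is not the constant hazard ratio to which a log-rank detectable effect refers.
- **Does the design lack 80% power at 1.35 altogether?** No. The unadjusted before/after comparison has it; the trend-adjusted one lacks it.
- **Does the protocol say that a null result would exclude 1.35?** No. *Methods* says that a null in objective 1 need not imply a null in objective 2, and the *Discussion* calls the study explorative. The risk of misreading is an inference.
- **Does any decision rest on the figure?** The cohort is every eligible Danish birth in the period, so neither recruitment nor data would change.

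These points limit the size and urgency of the finding. They do not restore 1.35 as the detectable effect of the adjusted analysis.

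**Conclusion.** The concern holds as a mismatch between the basis of the power statement and the planned analysis. In both readings of the planned spline, and also under a plain linear trend, power against a constant hazard ratio of 1.35 is below 80%. The direction is secure; the size depends on a model form that the protocol leaves open and on the assumptions listed in the check. Maternal age, smoking and other covariates were not modelled. With sample size fixed and the remedy a matter of reporting, this should be fixed but does not undermine the study.

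**What to change.** - In *Power calculation*, label 1.35 as the detectable hazard ratio of the unadjusted two-group comparison.
- In *Statistical analysis*, state whether a before/after term accompanies the spline, and which term or contrast tests the objective 1 hypothesis.
- Give the detectable effect for that model. For a before/after term plus spline it is about 1.7. For a continuous spline, give a detectable slope change and the effect shape assumed. The figure of about 1.45 should not be adopted unless a single linear trend is actually chosen.
- Add a sentence saying that a null trend-adjusted result does not exclude a hazard ratio of 1.35.

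The cost is one recalculation, a few sentences and a less favourable stated figure. No new data are needed. The protocol already undertakes to update itself if the analysis departs from it, so a route for the change exists.

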Conditional logistic regression analyses will be used in the 2nd objective to compare blood spot fatty acid levels between subjects with haematopoietic neoplasms and matched subjects who have not developed cancer. We will investigate industrial as well as ruminant TFA independently and mutually adjusted. Based on a priori consideration we will adjust for maternal and paternal age, smoking during pregnancy, birth weight and gestational age. Also, there might be regional and urban/rural differences in iTFA intake. Place of residence is available from Statistics Denmark, and can be included into analyses. Diets are usually different between families with higher and lower socioeconomic status and maternal socioeconomic status may influence intake of certain food products rich in trans-fat. Information on socioeconomic status, education and ethnicity is available from Statistics Denmark and can be controlled for.

As mentioned in the methods description, other fatty acids potentially related to haematopoietic neoplasms in children will be analysed in the DBS since our methodology allows a complete separation, identification and quantification of sixty fatty acids. We will therefore also investigate interactions between TFA and polyunsaturated fatty acids, and risk of haematopoietic neoplasms in children as well as association between polyunsaturated fatty acids and risk of cancer stratified by trans fatty acids.

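### Objective 2's least detectable OR of 1.35–1.75 assumes uncorrelated exposure within pairs, which is optimistic for iTFA because pairs share birth date and birthplace

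*Protocol article*

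**What the plan says.** The Power calculation section says of objective 2 that "we have a sample size of 700 cancer cases and 700 controls" and that, "assuming 80% power, the least detectable OR will be between 1.35 and 1.75, depending on the exposure among the controls", with control exposure running from 10% to 90%. It names Stata's power mcc command for 1:1 matched pairs. It gives no within-pair exposure correlation, and it states a significance level only for objective 1.

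Four other places bear on that correlation:

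- Study population (text on objective 2, after Fig. 2): controls are "individually matched for gender, exact date and year of birth", and also on parity and place of birth. Exact date or place may be relaxed if no match is found.
- Study population and Statistical analysis, objective 1: birth before or after 1 September 2004 is used as the proxy for fetal iTFA exposure.
- Discussion: "a previous study has shown a marked decline of average iTFA intake resulting in elimination after the ban".
- Statistical analysis, objective 2: "there might be regional and urban/rural differences in iTFA intake". The analysis is conditional logistic regression.

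**The concern.** A 1:1 conditional analysis learns only from differences within pairs. For a binary exposure, only discordant pairs count. For a continuous level, the variance of the within-pair difference is 2σ²(1 − ρ), where ρ is the within-pair correlation. Matching on something that determines exposure makes pair members more alike, so each pair carries less information.

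For iTFA, the protocol uses birth date as the exposure itself in objective 1. The objective 2 power figure nevertheless behaves as if birth date carried no information about exposure.

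This matters because objective 2 is the only part of the study that measures exposure in individuals, and the number of cases is limited by the register. The least detectable OR is what a reader will use to judge a null iTFA result. If it is too small, a null result will look more informative than it is.

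**Working it through.** **Inputs from the protocol.** There are n = 700 pairs, 80% power and control prevalence p0 from 0.1 to 0.9 (Power calculation). Births number 1,101,055 before and 276,422 after the cut date (Study population).

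**Assumptions.** Two-sided alpha of 5%, since none is stated for objective 2. The within-pair correlation phi is varied.

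**Formula (matched pairs).** Let p1 be exposure among cases, q0 = 1 − p0 and q1 = 1 − p1, with c = phi·√(p0·q0·p1·q1). The discordant-pair probabilities are

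- case exposed only: p10 = p1·q0 − c
- control exposed only: p01 = q1·p0 − c

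p1 is set so that p10/p01 = ψ, the conditional OR. With t = p10 + p01,

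z = [√(n·t)·(ψ/(1+ψ) − ½) − 1.96·½] ÷ [√ψ/(1+ψ)], and power = Φ(z).

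**Step 1: reproduce the stated figure.** Take p0 = 0.5, ψ = 1.35 and phi = 0. Then p1 = 0.574, t = 0.5, √350 = 18.71 and ψ/(1+ψ) − ½ = 0.0745. So z = (1.393 − 0.980)/0.494 = 0.836 and power is 79.8%.

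Solving for ψ at 80% power with phi = 0:

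| p0 | 0.1 | 0.2 | 0.3 | 0.4 | 0.5 | 0.6 | 0.7 | 0.8 | 0.9 |
|---|---|---|---|---|---|---|---|---|---|
| OR | 1.578 | 1.428 | 1.374 | 1.353 | 1.351 | 1.366 | 1.404 | 1.490 | 1.748 |

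The range 1.351–1.748 matches both stated ends. Working backwards, OR 1.35 at p0 = 0.5 implies phi = −0.004, and OR 1.75 at p0 = 0.9 implies phi = 0.004. An unmatched two-proportion calculation gives almost the same range, 1.351–1.757. With 700 pairs, phi = 0.1 does not fit (1.373–1.796). Nor does a one-sided 5% test, either at phi = 0 (1.306–1.630) or at phi = 0.2 (1.347–1.717).

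**Step 2: allow a positive phi (assumed values).**

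| phi | Least detectable OR, p0 10–90% | Power at OR 1.35, p0 = 50% |
|---|---|---|
| 0 | 1.35–1.75 | 80% |
| 0.1 | 1.37–1.80 | 76% |
| 0.2 | 1.40–1.86 | 71% |
| 0.3 | 1.43–1.93 | 65% |
| 0.4 | 1.48–2.03 | 58% |

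**Step 3: what birth date alone could induce.** Assume pairs split like births, w = 1,101,055/1,377,477 = 0.799, and that exposure prevalence is constant within each period. At overall prevalence 0.5:

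- *Post-ban births wholly unexposed.* Pre-ban prevalence is 0.5/0.799 = 0.626. Then phi = (0.799·0.626² − 0.25)/0.25 ≈ 0.25. The discordant fraction falls from 0.50 to 0.376, and √(700·0.376) = 16.2. So z = (1.208 − 0.980)/0.494 = 0.46 and power at OR 1.35 is 68%. The least detectable OR becomes 1.42.
- *Exposure only halves after the ban.* Pre-ban prevalence is 0.5/(0.799 + 0.201·0.5) = 0.556 and post-ban 0.278. Then phi = (0.799·0.556² + 0.201·0.278² − 0.25)/0.25 ≈ 0.05. Power is 78% and the least detectable OR is 1.36.

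The result depends heavily on the cut-off. With post-ban births wholly unexposed, overall prevalence 0.3 gives phi 0.11 and OR 1.40 (against 1.37). Overall prevalence 0.7 gives phi 0.59 and OR 1.69 (against 1.40).

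**The case against.** The strongest defence is that the figure is correct for its inputs and that the documents do not let anyone say how large phi is.

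- Elimination in the Discussion refers to average dietary intake, not to the biomarker. The same section allows that TFA from maternal fat stores may reach children born after the ban, and the Background describes a cap of 2 g per 100 g of oils and fats, not zero. The 68% power case is therefore an extreme, and the halving case costs little.
- Exposure is measured on a continuous scale and no cut-off is fixed. Cut-offs set within birth period would remove much of the calendar-driven correlation.
- The power statement is not specific to iTFA. Ruminant TFA and polyunsaturated fatty acids are also analysed, and the ban gives no reason to expect birth-date correlation for them.
- The evidence for place of birth is only that differences are possible.
- If the roughly 740 cases mentioned for objective 1 had been used, phi = 0.05 would give 1.35–1.74. The protocol states 700, however, and 0.05 is still close to zero.

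These points stand as limits on the size. None of them supports zero correlation for iTFA, and any positive correlation moves the figure in the same direction. A continuous analysis does not escape it either, since within-pair differences shrink too.

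A reader might also infer that 90% iTFA prevalence is impossible when about 20% of births follow the ban, so that prevalences above 80% should be dropped. The documents do not support this. It holds only if post-ban children count as wholly unexposed. A low cut-off with, say, nearly all pre-ban and half of post-ban children above it gives about 90%.

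**Conclusion.** The stated range of 1.35–1.75 rests on zero within-pair exposure correlation. For iTFA, that sits badly with the protocol's own matching scheme and with its use of birth date as the exposure proxy. The direction is firm: for any positive correlation, the least detectable OR is larger than stated and the power lower.

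The size is conditional on an assumed phi, on how exposure is categorised and on two-sided 5% testing. Over phi 0.1–0.4, the lower end of the range moves to between 1.37 and 1.48 and the upper end to between 1.80 and 2.03. The loss could be small if biomarker levels fell only partly after the ban or if cut-offs are set within birth period.

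It would be going too far to call this a calculation error, or to quote one corrected OR as the true one. The arithmetic is right for its inputs, and the fault is an unstated independence assumption. I rate it as a moderate point. It changes no estimate or test, but it does change how a null iTFA result should be read.

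**What to change.** In the Power calculation section:

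1. State the within-pair correlation and the significance level used for objective 2.
2. Rerun power mcc for iTFA with a positive correlation, for example 0.1–0.4, labelled as an assumption. Pilot blood-spot data would be a better basis if any exist.
3. Restate the least detectable OR for iTFA as the less favourable range. With 700 pairs and two-sided 5%, this is 1.37–1.80 at phi 0.1, rising to 1.48–2.03 at phi 0.4.
4. Keep 1.35–1.75, marked as assuming phi = 0, only for fatty acids not expected to vary with birth date.
5. Keep the full 10–90% prevalence range, since no cut-off is fixed.

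The cost is one rerun, a few sentences and a less favourable published figure. Sample size, matching and analysis need not change.
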